#### Quantitative Bone Formation Evaluation

CBCT scans obtained before extraction, 3 months and 6 months post extraction were analyzed using Digora software (Digora for Windows 2.8.107.458 Network Client, Soredex Orion Corporation) to evaluate bone density and formation characteristics. The region of interest, corresponding to the socket preservation and grafting site, was identified based on the grafted area. The view was adjusted axially to align with the angulation of the alveolar ridge. The contours of the crestal bone were delineated, taking into account any apical recession of the alveolar crest on the buccal or lingual aspect. The buccolingual width of the alveolus was then measured 2 mm below the alveolar crest level before tooth extraction and at the follow-up time point. Changes in ridge width were calculated by subtracting the preoperative measurements from the postoperative ridge width measurements.

#### Monitoring

Continuous monitoring will be conducted by internal monitors from the Hasanuddin University Faculty of Medicine’s Ethics and Research Committee to ensure the study’s compliance with ethical guidelines. A separate Data Safety Monitoring Board will not be established as the study is associated with minimal risk. However, an annual safety report will be submitted to the Medical Research Ethics Committee of the Faculty of Medicine at Hasanuddin University.

### Statistical Analysis

Statistical analysis will be performed using SPSS 16.0 (IBM Corp). Student *t* test will be used to analyze the difference between groups and different follow-up points. The statistical significance level will be set at a *P* value of .05 or lower.

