### Study Design

This prospective control clinical trial will be conducted at a single center and will involve 30 targeted extraction sockets after the removal of impacted mandibular third molars. This case is chosen as it represents a common scenario requiring extraction and often involving the removal of a significant amount of bone, making it an ideal model for studying human alveolar bone loss for socket preservation. The study aims to evaluate the efficacy of a high-purity α-CSH bioceramic (CaSO_4_·0.5H_2_O), synthesized from calcium sulfate dihydrate (CSD) without the use of chemical reagents, as a bone graft material in the alveolar bone loss case.

The 30 extraction sockets will be randomly assigned into 2 groups: 15 will receive α-CSH as a bone graft, while the other 15 will not receive any graft material. The main end point will be evaluated 6 months into the procedure. During follow-up visits, any adverse events or serious adverse events will be carefully documented, and clinical assessments will be conducted as specified in the “intervention section.” All patients will undergo regular monitoring through clinical examinations, radiographs, lab tests, and any additional necessary procedures. Ultimately, the study will publish a comprehensive report on the feasibility and potential efficacy of the α-CSH approach in promoting bone formation, regardless of the outcome.

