### Sample Size

As this study focuses on feasibility rather than achieving statistical significance, formal power calculations were not conducted prior to its initiation. Instead, the emphasis lies on assessing safety, feasibility, and generating preliminary data.

With no prior data on the use of this bone graft material in humans, the sample size was determined based on practical considerations, including resource availability, feasibility of recruitment within the study timeline, and ethical concerns regarding participant risk exposure. The aim was to enroll a sample size, allowing for meaningful observations and providing valuable preliminary insights into safety and efficacy.

Furthermore, following a common rule of thumb for pilot studies, which typically suggest around 30 participants, we decided on a sample size of 30 extractions, with 15 extraction sockets in each group. The number of sockets per patient varies based on individual clinical circumstances. This sample size was deemed appropriate for assessing safety, feasibility, and generating preliminary efficacy data.

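### Preoperative ridge width is used only to form a change score for a t test; adjusting for it as a covariate would usually be more precise and would correct chance baseline imbalance, and within-arm tests over time cannot show acceleration

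*Protocol article*

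**What the plan says.** The Statistical Analysis section of the protocol article gives one method, Student's t: "test will be used to analyze the difference between groups and different follow-up points". It mentions no covariate and no model for repeated visits, and it sets a P threshold of .05.

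Under Quantitative Bone Formation Evaluation, buccolingual width is "measured 2 mm below the alveolar crest level before tooth extraction and at the follow-up time point", and then: "Changes in ridge width were calculated by subtracting the preoperative measurements from the postoperative ridge width measurements". The scans are taken at three times: "CBCT scans obtained before extraction, 3 months and 6 months post extraction were analyzed using Digora software". Table 1 requires the preoperative CBCT, so the baseline value is planned for every socket.

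Study Design fixes the main time: "The main end point will be evaluated 6 months into the procedure". On size, "we decided on a sample size of 30 extractions, with 15 extraction sockets in each group", and "formal power calculations were not conducted prior to its initiation".

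The Statistical Analysis section does not say which variable is tested. Change in width is the natural reading, because it is the only derived width variable that the article defines.

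**The concern.** Subtracting the preoperative value fixes the slope of follow-up on baseline at 1. Unless the true slope is 1, part of any chance baseline difference stays in the arm comparison, and the variance is larger than it need be. With 15 sockets per arm and no power calculation, the estimate and its interval are the main product of the efficacy part, so precision matters.

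The second issue is what the tests can answer. The Abstract's conclusions and the Discussion hypothesise that α-CSH speeds bone formation. A test between follow-up points within one arm shows only whether that arm changed, and ungrafted sockets may change as well. A significant result in one arm beside a non-significant one in the other is not a comparison of arms.

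**Working it through.** **Inputs from the protocol article.** 15 sockets per arm (Sample Size); scans before extraction and at 3 and 6 months; main time 6 months. The total of 30 comes from a rule of thumb for pilot studies, so there is no planned calculation to reproduce.

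**Assumptions.** Equal SD (s) of width before and after; pre-post correlation ρ, not given, taken from 0.3 to 0.95; independent sockets; a linear relation to baseline; two-sided 5% level.

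**Variance of the arm difference.**
- Change score: (2/15) · s² · 2(1−ρ)
- ANCOVA: (2/15) · s² · (1−ρ²) · [1 + 1/(2·15−4)]. The bracket is 1 + 1/26 = 1.038, the cost of estimating the slope.
- Ratio, ANCOVA to change score: 1.038 · (1+ρ)/2. At ρ = 0.5 this is 1.038 × 0.75 = 0.779.

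The CI width ratio also uses t on 27 degrees of freedom for ANCOVA and 28 for the change score. The shift is the effect on the change-score contrast of a 0.5 SD baseline difference, 0.5(1−ρ), working against the arm that starts wider. The last column is √[(2/15) · 2(1−ρ)].

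| ρ (assumed) | Variance ratio | Equivalent sockets, 30/ratio | CI width ratio | Shift (SD) | SE of change-score contrast (SD) |
|---|---|---|---|---|---|
| 0.3 | 0.675 | 44.4 | 0.823 | 0.35 | 0.43 |
| 0.5 | 0.779 | 38.5 | 0.884 | 0.25 | 0.37 |
| 0.7 | 0.883 | 34.0 | 0.941 | 0.15 | 0.28 |
| 0.8 | 0.935 | 32.1 | 0.968 | 0.10 | 0.23 |
| 0.9 | 0.987 | 30.4 | 0.995 | 0.05 | 0.16 |
| 0.95 | 1.012 | 29.6 | 1.008 | 0.025 | 0.12 |

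**Break-even.** Setting 1.038 · (1+ρ)/2 = 1 gives ρ = 0.926; with the lost degree of freedom it is about 0.92. As ρ approaches 1 the variance loss approaches 4%.

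**Simulation check.** With independent sockets (6000 runs each), the variance ratios were 0.761, 0.939 and 1.006 at ρ = 0.5, 0.8 and 0.95, in line with the formula.

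**Chance imbalance.** The SD of the baseline mean difference is √(2/15) = 0.365 SD. Then 0.5/0.365 = 1.37, and the two-sided normal tail is 0.171, about 17%.

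**If the t test uses raw follow-up width instead.** The ratio is 1.038 · (1−ρ²): 0.779, 0.530, 0.374 and 0.197 at ρ = 0.5, 0.7, 0.8 and 0.9. Adjustment then gains more the higher ρ is.

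**More than one socket per patient.** Sample Size says that the number of sockets per patient varies. In a simulation with seven two-socket patients and one single-socket patient per arm, both sockets in the same arm and an assumed intra-patient correlation of 0.5, type I error was about 0.11 for the t test and for ANCOVA alike. Baseline adjustment does not cure clustering.

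**Acceleration.** Let D3 and D6 be the arm differences at 3 and 6 months. An arm-by-time term fitted to these two visits estimates D6 − D3. If the graft gives an early gain that persists, D6 − D3 is zero; if controls catch up, its sign reverses. Early acceleration therefore bears on D3.

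**The case against.** The strongest reply is that this is a preference. In a randomised comparison the change-score t test is unbiased, the trial is a pilot that disclaims power, and covariate adjustment is often left to an analysis plan. Most of this stands, and it limits the point to efficiency and chance imbalance. It does not remove the point, because the article names its test, sets a significance threshold and promises preliminary efficacy data.

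The size of the gain is also open to challenge. A width re-measured at the same site may correlate highly, and near 0.9 there is almost nothing to gain over a change score. That stands. So does the observation that a 0.5 SD imbalance moves the estimate by less than one standard error throughout the range shown. The 17% depends on 30 independent sockets: clustering within one arm would raise it, and splitting a patient's sockets between arms could lower it. Study Design randomises sockets and Randomization and Blinding randomises participants, so the article does not settle which applies.

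Finally, the wording on follow-up points may mean group comparisons at each visit, and a comparison between visits could be a paired test. Using the same socket twice is no defect in itself. The objection to within-arm tests applies only if they are offered as evidence of a graft effect.

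**Conclusion.** The point holds as a moderate, inexpensive improvement. On the natural reading that change in width is tested, adjusting for preoperative width cuts the variance by about 22%, 12% and 6% at assumed correlations of 0.5, 0.7 and 0.8. It makes little difference around 0.9 and costs about 1% at 0.95. It also corrects chance imbalance in measured width, provided the relation to baseline is linear.

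Three stronger readings are tempting and are not supported:
- **That the planned test is biased or invalid.** It is unbiased over randomisations; only the estimate given a particular imbalance is shifted.
- **That adjustment is free or always gains.** The large-sample ratio (1+ρ)/2 never exceeds 1, but it omits the 4% slope cost at 15 per arm, and the article gives no correlation.
- **That an arm-by-time term measures speed of healing.** With outcomes only at 3 and 6 months it measures how the arm difference changes between those visits.

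The conclusion on within-arm tests needs no assumed correlation: they do not compare the arms.

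**What to change.** State in Statistical Analysis that the arms are compared on 6-month ridge width with preoperative width as covariate, reporting the adjusted difference and its 95% CI. Do the same at 3 months, and name the 3-month arm contrast as the one that bears on early acceleration. Do not use within-arm tests over time as evidence of effect.

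If one model covers both visits, include arm, time, arm-by-time, baseline and baseline-by-time, and account for repeated scans of a socket. Where patients contribute more than one socket, account for patient too, and use a small-sample degrees-of-freedom correction. Separate patient and socket random effects may not be identifiable if most patients give one socket, so the structure should be kept as simple as the data allow.

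This does not decide which variable is the main end point. Study Design fixes only its time, and the Discussion lists other bone measures. The same adjustment applies to any of them that has a preoperative value.

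Cost: analysis wording, one or two degrees of freedom and about 4% variance inflation from estimating the slope. No new scans or visits are needed.

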### Outcomes

#### Feasibility Assessment

The assessment of α-CSH safety in the present context will focus on the occurrence of serious adverse events. To deem α-CSH as safe, it should not result in a higher frequency of adverse events compared to standard treatment (without socket preservation). Additionally, any adverse events that do arise should be manageable through established noninvasive procedures such as analgesics and antibiotics. The evaluation of safety will play a crucial role in determining the suitability and viability of α-CSH in the study.

Feasibility evaluation was conducted using intraoral clinical examination and photographs to assess potential complications such as inflammation, infection, dehiscence, and graft loss. Graft loss will be evaluated in the early postoperative period, within the first week, and late postoperative period. The progress of wound healing at the surgical sites will be assessed with the Landry wound healing index [23]. This index considers factors such as the color of the soft tissue (pink or red), presence of suppuration, amount of bleeding, presence of granulation tissue, and exposure of connective tissue. Based on these criteria, the healing process was categorized into 5 distinct categories, namely very poor, poor, good, very good, and excellent [23]. Patients were also asked about any pain in the surgical site or adjacent areas during the follow-up period.

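### Student's t, the only test named, is stated without restriction and does not suit the 5-level healing index or the adverse-event and complication frequencies

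*Protocol article*

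**What the plan says.** The Statistical Analysis section of the protocol article names Student's t and says that the "test will be used to analyze the difference between groups and different follow-up points". Significance is set at a P "value of .05 or lower". No other method is named, and the test is not tied to any outcome.

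The Feasibility Assessment section describes outcomes of a different kind. For the Landry index, "the healing process was categorized into 5 distinct categories, namely very poor, poor, good, very good, and excellent". For safety, the criterion for the graft is that "it should not result in a higher frequency of adverse events compared to standard treatment". The same section lists complications such as infection, dehiscence and graft loss, which are naturally recorded as present or absent.

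The section on quantitative bone formation defines a continuous measure, the change in ridge width on CBCT.

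On size, the Sample Size section says "we decided on a sample size of 30 extractions, with 15 extraction sockets in each group", and that "formal power calculations were not conducted prior to its initiation".

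**The concern.** Read literally, the single rule covers every comparison between groups, but it fits only the CBCT measures. Applied to the Landry index, a t test compares means of scores 1 to 5 and so treats the steps between categories as equal. Applied to yes/no events in groups of 15, it relies on a normal approximation, and it breaks down when nobody has an event.

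Healing, complications and adverse events are what the feasibility and safety statements will rest on. The safety criterion is itself a comparison of frequencies between groups. With counts this small, the choice of method can decide whether a difference is called significant, so the method should be settled before the data are seen.

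**Working it through.** **1. Inputs.** From the article: 15 sockets per group and a significance level of 0.05. Assumed here: two-sided tests, independent sockets, and all category distributions and event rates. The article gives no effect size, event rate or power, so the only figure of its own to reproduce is 15 + 15 = 30, which agrees.

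**2. Landry index.** Scores 1 (very poor) to 5 (excellent) were simulated, with 20,000 trials per scenario. The second group was shifted by dividing the cumulative odds of being at or below each category by an odds ratio (OR). The pooled t test was compared with the tie-corrected Wilcoxon-Mann-Whitney test.

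| Assumed control distribution, very poor to excellent (%) | Power at OR 5: t / rank | Power at OR 8: t / rank |
|---|---|---|
| 10, 20, 40, 20, 10 | 0.646 / 0.649 | 0.848 / 0.851 |
| 35, 10, 10, 10, 35 | 0.594 / 0.602 | 0.769 / 0.783 |
| 2, 8, 25, 40, 25 | 0.599 / 0.618 | 0.788 / 0.814 |
| 5, 5, 10, 30, 50 | 0.450 / 0.511 | 0.611 / 0.684 |
| 2, 3, 5, 20, 70 | 0.276 / 0.336 | 0.355 / 0.433 |

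With no difference between groups (OR 1), the t test rejected in 0.042 to 0.051 of trials. The largest loss in the table is 0.433 − 0.355 = 0.078, about 8 points. A further set of assumed shifts reached about 9 points, and the rank test never cost more than about 2. One assumed pattern with a heavy poor tail gave 26% power for t against 53% for the rank test. That last pair shows the direction only and is not an estimate for this trial.

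**3. No events in either group.** Both group variances are then zero, so t = 0/0 and its interval has zero width. With event risk p per socket, the chance is (1 − p)^30:

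- p = 1%: 0.99^30 = 0.74
- p = 2%: 0.98^30 = 0.55
- p = 5%: 0.95^30 = 0.21

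An exact method still says something: 0/15 has an upper two-sided 95% limit of 1 − 0.025^(1/15) = 0.218 for that group's risk.

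**4. A few events.** Take 4/15 against 0/15. The within-group variances are 4 × 11/(15 × 14) = 0.2095 and 0, so the pooled variance is 0.1048. Then SE = √(0.1048 × 2/15) = 0.1182 and t = 0.2667/0.1182 = 2.26 on 28 degrees of freedom, P = 0.032. Fisher's exact test gives 2 × C(15,4)/C(30,4) = 2 × 1365/27405 = 0.100.

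| Events | t test P | Fisher P |
|---|---|---|
| 4/15 v 0/15 | 0.032 | 0.100 |
| 5/15 v 0/15 | 0.013 | 0.042 |
| 6/15 v 1/15 | 0.031 | 0.080 |
| 7/15 v 2/15 | 0.048 | 0.109 |

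**5. Which test is at fault in step 4?** Enumerating all 15 v 15 tables, the t test's type I error is 0.005 at a common rate of 5%, 0.025 at 10% and at most 0.055 (near 28%). Fisher's is at most 0.017 at common rates of 5%, 10%, 20%, 30% and 50%. Barnard's unconditional exact test gives P = 0.043 for both 4/15 v 0/15 and 6/15 v 1/15. So much of the gap is Fisher's conservatism. It shows in power too, t against Fisher: 0.446 v 0.275 for 5% v 30%, 0.510 v 0.325 for 10% v 40%, and 0.726 v 0.536 for 10% v 50%.

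**The case against.** The strongest reply is that the article does not say the t test will be used on the Landry index or on adverse events. The quantity it defines as a change between time points is ridge width, for which a t test is a suitable kind of test. The safety statement is a criterion, not a declared hypothesis test, and descriptive reporting would be compatible with it. A condensed article may leave methods for such outcomes to a fuller plan that is not shown.

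Much of this stands. The article does not assign the t test to these outcomes, and the absence of further named tests is not in itself a fault. What remains is that the one rule it does state carries no limit, and followed as written it covers outcomes that it does not fit.

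A reader might go further and infer that the t test wastes power in this trial. The documents do not support that. Against a rank test the loss is nil to small unless scores pile up at one end, and against Fisher's test the t test has more power, not less. The Sample Size section also disclaims any power target, so none is missed. Nor can the t test be called generally unreliable for small counts, since its type I error reached at most 0.055.

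**Conclusion.** The point holds as a mismatch between the only named test and the type of the healing and safety outcomes. For the index, the t test is valid in error rate but less efficient when scores cluster at the top: about 0 to 9 points of power under the proportional-odds shifts assumed, more with a heavy poor tail. For events, the clear failure is the case of none in either group, which is likely if the risk per socket is 1% or 2%. The different P values in step 4 show that the method should be fixed in advance. They do not show that the t test is wrong.

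The 6-month CBCT comparison is unaffected. All distributions and rates are assumptions. The calculations also treat sockets as independent, whereas the Sample Size section says "The number of sockets per patient varies based on individual clinical circumstances".

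**What to change.** Amend the Statistical Analysis section in three respects:

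- Limit the t test to the continuous CBCT measures.
- Compare the Landry index between groups by a rank test or a proportional-odds model.
- Report adverse events and complications as counts per group with an exact 95% confidence interval for the risk difference, and base the safety conclusion on that interval.

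If a test for events is also wanted, name an exact one. State that Fisher's is conservative and less able than the t test to detect an excess of harm, so that a non-significant result is not read as evidence of safety.

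The cost is two or three sentences and no further patients. These are standard methods, though it should be checked that the named software produces the exact interval. Where a patient contributes more than one socket, these methods need a version that allows for it, as does the t test.

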### Amendments

Any significant changes that arise during the course of the trial will be promptly reported to the ethical committee and the relevant authority. This ensures the participant’s safety and well-being, maintains the trial’s integrity, and upholds its scientific value.

### Posttrial Care

In order to ensure the safety of participants and monitor any potential long-term adverse effects of the α-CSH graft material, secondary follow-up will be conducted for all participants at 1 and 2 years. This extended follow-up period will allow for thorough evaluation and observation of any potential late-onset complications or concerns related to the use of α-CSH.

## Results

The project secured funding in 2022 and is currently in the enrollment phase, with participants being recruited and awaiting the follow-up period. The initial findings of the study are expected to be submitted for publication in late 2024.

The trial’s outcomes will be disseminated through diverse strategies, encompassing academic publications, research reports, and participation in international conferences. The results pertaining to the primary objective will be detailed in a primary manuscript designated for submission to a distinguished, high-impact, peer-reviewed journal.

## Discussion

This clinical investigation serves as the inaugural examination of human subjects to evaluate the feasibility and effectiveness of α-CSH in the regeneration of alveolar bone. Our hypothesis posits that the incorporation of α-CSH may significantly accelerate bone formation within fresh sockets, leading to a rapid restoration of bone height while mitigating the drawbacks associated with autogenous bone graft harvesting.

In dentistry, bone grafts and substitute materials are commonly used to regenerate missing hard tissue structures [24,25]. In recent years, there has been a growing interest in the use of bone graft substitutes, driven by concerns over potential immune reactions associated with allografts [1,2,18]. Challenges remain, particularly regarding graft versus host responses associated with nonautograft-derived materials [24,26]. Furthermore, one significant obstacle encountered is the limited research conducted on the safety and effectiveness of newer bone grafting materials [26,27]. Existing information about these materials is primarily derived from case reports or experimental animal models, which may raise concerns about the reliability of such data [8,26,28]. It is crucial to conduct more standardized, well-documented preclinical and clinical studies to gain a comprehensive understanding of the clinical viability and advantages of each material. This will facilitate the introduction of a wider range of commercially available products based on reliable evidence.

The α-CSH, a substance with remarkable characteristics such as high self-setting strength, excellent osteoinductive properties, biocompatibility, and angiogenesis capabilities, has emerged as a popular alternative to traditional bone grafts [29-31]. Previous in vitro and in vivo studies conducted by our team have demonstrated the ability of α-CSH to promote angiogenesis and enhance osteogenesis [14,17,29]. Given the strategic development of α-CSH as a potential biomaterial for bone regeneration, it holds promise as a unique biocomposite bone graft material to be investigated in this study [30,31]. This clinical trial represents a pioneering effort to investigate the potential regenerative capacity of α-CSH in the context of alveolar bone loss, specifically in post-extraction sockets following an odontectomy procedure.

This study aims to provide initial evidence regarding the viability of α-CSH as a bone graft material, specifically its suitability for human transplantation. The effectiveness of the intervention will be evaluated by measuring bone parameters such as bone volume, graft volume, and bone height over a 6-month period. In previous studies, histomorphometric and histological analysis has typically been used to assess the new bone formation and remineralization of the grafted sites [25,32,33]. Unfortunately, it is not feasible in the case of postodontectomy third molar due to an ethical concern for the second operation. Instead, we expect that both panoramic and CBCT imaging will provide a clear visualization of bone volume and density in the evaluated area as it has been used in previous bone regeneration studies [24,34,35]. By using radiographic techniques, we can evaluate bone production and quantify various parameters associated with bone formation [34-36]. The anticipated outcomes of this study will have significant scientific and clinical implications, enhancing our understanding of the feasibility and early efficacy of α-CSH. These findings can guide the approach to socket preservation following tooth extraction, particularly in cases involving bone augmentation for implant placement. Furthermore, this research has the potential to contribute to the development of biomaterials for clinical use, advancing the field and ultimately improving patient outcomes.

Our research encounters several limitations that warrant consideration, including the challenge of recruiting patients who meet our stringent inclusion and exclusion criteria, which poses a significant hurdle. Relying solely on hospital patients for recruitment may limit the generalizability of our findings, underscoring the need for broader sampling strategies in future studies. Additionally, the absence of previous studies to estimate sample size leaves us navigating uncharted territory, potentially impacting the precision and adequacy of our sample size determination. Despite these limitations, our study presents compelling initial data on the accelerated bone formation observed with α-CSH in fresh sockets. These findings will provide a foundation for further exploration and offer valuable insights that can inform the design and execution of larger clinical trials or studies in the future.

This protocol outlines our approach to assessing the feasibility and initial efficacy of α-CSH as a promising grafting material for alveolar bone loss, specifically in cases involving postodentectomy mandibular third molars. We aim to evaluate the potential of α-CSH as a graft material and determine its suitability in this clinical scenario.

